#### Youth engagement

A 19-item *Engagement Questionnaire* devised by the research team will be utilized to determine the youth’s use of mental health services, medication use, and potential barriers to service use. The items regarding barriers to and for service use items are responded to on a 7-point scale where 1 reflects ‘not at all important’ and 7 reflects ‘a very important factor’. *The University of Rhode Island Change Assessment Scale Readiness to Change Questionnaire- DELTA Project (URICA-D)* is a 12-item scale [44], and will be administered to youth with items adapted to reflect youth readiness to change in relation to their depression instead of in relation to alcohol and other drug problems. In addition, youth engagement will be assessed via their attendance or not at the group with their family when invited.

### Reimbursement

The questionnaire will be completed by the youth experiencing depressive symptoms, and with parental consent, their siblings (aged 12 and over) who reside in the family home. At each of the three time points, youth completion of a KID-SCID telephone interview and a full questionnaire will be reimbursed with AU$15 vouchers, while the siblings will be reimbursed with AU$10 vouchers for each questionnaire completed.

### Sample size and power

The trial aims to recruit a total of *n* = 160 participants. Based on pilot work and previously conducted clinical trials of family-based interventions compared to treatment-as-usual conditions, it has been estimated that it is possible to generate an effect size of *d* = 0.63 in reduction of mental health symptoms, which is equivalent to 14% increase in the odds of remission [45]. Out pilot data also indicates that treatment type by time interaction is able to produce up to 50% remission in depression diagnosis, over and above treatment type. With an alpha of 0.05 and power level of 0.90 for two-tailed tests, intraclass correlation coefficient (ICC) of 0.17 for within therapy group variation (estimated from our pilot data), and estimated 10% of variation in the main outcome accounted for by other variables in the model (treatment arm, time, parental socioeconomic status), the minimum sample size required equates to *n* = 57 per treatment arm. Based on pilot studies, an attrition rate of 20 to 25% is anticipated. Therefore, a minimum of 80 participants into each of the two treatment conditions will be recruited. Comparisons will be undertaken between those who drop out and those who are retained in order to assess for attrition bias.

With respect to our secondary hypotheses, anticipated final sample size of 114 individuals, will also allow us to detect small effect size (d = 0.23) for the treatment arm by time interaction for continuous outcomes, with 90% power and alpha level of 0.05, assuming ICC of 0.20 for within-person (between-assessment) and ICC of 0.07 for within therapy group variation (estimated from our pilot data).

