### Aims and hypotheses

The primary aim of the trial is to evaluate the efficacy of the two interventions as: (a) treatments for youth mental health problems and (b) as methods of engaging youth in treatments. The secondary aims will include: (c) to build capacity and increase service integration across several service delivery sectors by providing evidence based intervention programs for youth and their families; (d) to influence national and state government policy on the use of family based approaches in the field of youth mental health; and (e) make use of the study partnerships for national promotion and dissemination of family-based treatment models for youth mental health.

The primary study hypothesis is that youth in the BEST MOOD intervention will demonstrate significantly greater rates of remission of depressive disorders (major, minor, or dysthymia), than youth in the PAST intervention. Secondary hypotheses include: (a) that parental and youth mental health and relationships will improve in response to both interventions, but significantly more so in response to BEST MOOD; (b) that greater treatment engagement for youth will be associated with greater improvements in youth mental health outcomes; and (c) that youth in the BEST MOOD condition will report greater treatment engagement than youth in the PAST condition.

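### The planning effect d = 0.63 is said to equal a 14% increase in the odds of remission; it corresponds to an odds ratio of about 3

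*Protocol article*

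**What the plan says.** The Overview section makes remission of depressive disorder, a yes/no outcome, the primary outcome. The Statistical analysis plan section analyses repeated binary data with a mixed logistic regression. The treatment effect on the primary outcome will therefore be estimated as an odds ratio.

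The Sample size and power section states the planning effect as a standardized difference of d = 0.63 and translates it in the same sentence: "in reduction of mental health symptoms, which is equivalent to 14% increase in the odds of remission". The next sentence adds a pilot figure of up to 50% remission, attributed to the treatment-by-time interaction. It gives no control-arm rate.

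The calculation then uses these inputs:

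- "With an alpha of 0.05 and power level of 0.90 for two-tailed tests"
- "intraclass correlation coefficient (ICC) of 0.17 for within therapy group variation"
- "estimated 10% of variation in the main outcome accounted for by other variables in the model"

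It concludes that "the minimum sample size required equates to *n* = 57 per treatment arm". With anticipated attrition of 20 to 25%, 80 per arm are to be recruited.

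**The concern.** A standardized difference of 0.63 is a medium-to-large effect. A 14% increase in the odds is a very small one. The two cannot be equivalent, yet the sentence offers the second as a translation of the first. The digits suggest a slip, because the correct log odds ratio is 1.14, which could have been read as an odds ratio of 1.14. A digit lost from 214% would fit equally well. Either explanation is an inference, and the point does not depend on it.

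What is at stake is interpretation. The 14% is the only between-arm target expressed on the scale of the primary analysis. A reader who relies on it would take the trial to have 90% power for a modest benefit. A non-significant result could then be read as evidence against modest benefits, which a trial of this size cannot provide.

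**Working it through.** **Inputs.** From Sample size and power: d = 0.63, stated odds increase 14% (OR 1.14), two-sided alpha 0.05, power 0.90, ICC 0.17, 10% of variance explained, n = 57 per arm. Not stated, so assumed: control remission of 20 to 50%, no clustering in the binary calculations, and the cluster size used in step 1.

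**1. Which figure lies behind the 57?** Comparing two means with d = 0.63:

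n = 2 × (1.960 + 1.282)² / 0.63² = 52.9, i.e. 53 per arm (53.9 with the t distribution).

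Multiply by a design effect of 1 + (2 − 1) × 0.17 = 1.17 (cluster size 2 assumed) and by 1 − 0.10 = 0.90 for covariates:

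- t-based: 53.9 × 1.17 × 0.90 = 56.8, i.e. 57
- normal approximation: 52.9 × 1.17 × 0.90 = 55.8, i.e. 56

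So 57 can be reached from d = 0.63. Step 4 shows that it cannot be reached from OR 1.14.

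**2. Converting d to an odds ratio.**

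- Logistic: ln(OR) = d × π/√3 = 0.63 × 1.8138 = 1.143; OR = exp(1.143) = 3.14; odds increase 214%.
- Cox: ln(OR) = 1.65 × 0.63 = 1.04; OR = 2.83; odds increase 183%.

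**3. Converting the stated 14% back to d.** ln(1.14) = 0.131.

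- Logistic: 0.131 / 1.8138 = 0.072
- Cox: 0.131 / 1.65 = 0.079

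The size of the discrepancy depends on the scale. Under the logistic conversion it is 3.14/1.14 = 2.75-fold on the odds ratio, 1.143/0.131 = 8.7-fold on the log odds, and 214/14 = about 15-fold on the percentage increase in the odds.

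**4. What 57 per arm would do for OR 1.14.** Treated rate p₂ = OR × o / (1 + OR × o), where o = p₁/(1 − p₁). Sample size per arm for two proportions at 90% power, with p̄ the mean of the two rates:

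n = [1.960 × √(2p̄(1 − p̄)) + 1.282 × √(p₁(1 − p₁) + p₂(1 − p₂))]² / (p₂ − p₁)²

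| Control remission | Treated, OR 1.14 | n per arm, OR 1.14 | Treated, OR 3.14 | Difference, OR 3.14 |
|---|---|---|---|---|
| 20% | 22.2% | 7,364 | 43.9% | 23.9 points |
| 30% | 32.8% | 5,686 | 57.3% | 27.3 points |
| 40% | 43.2% | 5,041 | 67.6% | 27.6 points |
| 50% | 53.3% | 4,903 | 75.8% | 25.8 points |

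Two-sided power at 57 per arm for OR 1.14, for example at 30%: SE = √((0.210 + 0.2205)/57) = 0.087; 0.028/0.087 = 0.325; power = Φ(0.325 − 1.960) + Φ(−0.325 − 1.960) = 0.051 + 0.011 = 0.062. Over control rates of 20 to 50% the power is 5.9 to 6.4%, hardly above the 5% error rate.

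**5. Could 14% mean percentage points?** OR 3.14 gives 24 to 28 points for control rates of 20 to 50%. It gives 14 points only at control rates near 8.5% or 78%.

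**The case against.** The strongest reply is that the 14% is a gloss and does no work. The sentence gives d = 0.63 first, step 1 shows that 57 can be built on it, and correcting the gloss changes no number that governs recruitment. This stands, and it limits the point to the stated target effect. A reader might infer that the 57 is miscalculated or that the trial was sized for the wrong effect. The article does not support that inference from this error alone. Whether a symptom-scale d is the right basis for sizing a binary outcome, and what cluster size was used, are separate questions.

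A second reply is that the 14% may mean percentage points. The text says odds, and no control rate is given. The reading fails over 20 to 50% but would fit near 8.5% or 78%. It is therefore too strong to say that no reading could reconcile the figures. Nothing in the article points to either of those control rates, so the reading does not rescue the sentence as printed.

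Third, the sentence about up to 50% remission also speaks on the remission scale and suggests a large effect. That is fair. The 14% is not the only remark about remission, but it is the only between-arm target on the odds scale, and the 50% figure cannot be turned into an odds ratio without a control rate.

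Fourth, a careful reader would notice the conflict, since the same section calls d = 0.23 small. That is also fair: misreading is a risk, not a certainty. But the reader who notices still has to guess which figure is meant.

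The source cited for the equivalence is not available here. The conclusion does not need it, because both standard conversions contradict the sentence.

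**Conclusion.** The point holds as an error in the stated target effect. A d of 0.63 corresponds to an odds ratio of 2.8 to 3.1, depending on the conversion, and the article does not correct the 14% elsewhere. The conversion itself rests on no assumption about remission rates. The consequences do: about 6% power at 57 per arm and about 4,900 to 7,400 per arm needed for OR 1.14 assume control remission of 20 to 50% and ignore clustering. Clustering with a positive ICC would raise the required numbers further.

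Calling the error an order of magnitude is fair for the log odds or the percentage increase, but not for the odds ratio itself, where it is 2.75-fold. The finding does not show that the sample size of 57, or the recruitment target of 80 per arm, is wrong. The primary hypothesis under Aims and hypotheses contains no error on this point.

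**What to change.** In Sample size and power, replace the 14% statement with an odds ratio of about 3 (2.8 to 3.1 depending on the conversion), and name the conversion used. Add the two remission proportions that this implies from the pilot control rate. If that rate were 30%, for example, the odds would be 0.30/0.70 = 0.4286; multiplied by 3.14 they become 1.344, a treated rate of 57%. If 14 percentage points were intended, say so and give the control rate that makes it consistent with d = 0.63. Add a sentence that a non-significant result does not exclude effects smaller than the planning effect.

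The cost is one or two sentences. Recruitment, conduct and analysis do not change. The stated target becomes less favourable, because it will be seen to be a large effect.

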## Methods/Design

### Overview

The study is a multi-center, double-blind, randomized controlled trial comparing two group interventions: the BEST MOOD program and a treatment-as-usual supportive parenting program known as Parenting Adolescents Support Training (PAST). Both interventions are for families of youth who present with a unipolar mood disorder, here defined as major or minor adolescent depression or dysthymia. In both treatment conditions, families receive eight sessions of treatment delivered over two hours per week. The trial will run across several sites in both metropolitan Melbourne and the regional Victorian city of Geelong. Families will be recruited primarily from the intake service of a large government run mental health service in the eastern region of Melbourne (Eastern Health’s Child and Youth Mental Health Service; CYMHS), but community referrals will also be accepted from schools and community based health and mental health services, and via promotion of the study at community forums. At the completion of the interventions, face-to-face interviews will be conducted to better understand the level of engagement of participants with the treatment following intake/assessment. The aims of the qualitative component of the study are to explore the phenomena of not taking-up treatment, discontinuing treatment after commencement, completing treatment and benefiting from treatment, and the perceived influencing factors on these outcomes.

The primary outcome measure will be rates of remission of depressive disorder (major, minor, or dysthymia), according to a structured diagnostic clinical assessment, utilizing modules from the Structured Clinical Interview for *DSM-IV Childhood Diagnoses* KID-SCID; [28]. The secondary outcome measures will include: adolescent mental health (parent and self-reported), parent mental health, the young person’s level of engagement with mental health services, the parent-child relationship, and the therapist-client working alliance. Psychologists, social workers, and postgraduate psychology students who will be trained and supervised in one of the interventions for an equivalent amount of time, will deliver treatment. Therapists and assessors are blinded to the content of the alternate intervention, and are blinded to whether they are delivering the experimental or control condition in the study.

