### Statistical analysis plan

Repeated measures binomial data will be analyzed over three time points using a binary logistic regression within the Generalized Linear Mixed Model (GLMM). The model will be fitted in STATA (xtmelogit). For any continuous-scale data we will use a linear mixed model approach in STATA. For both types of data we will explore variance-covariance structures for the evaluations within an individual. Clinical significance and an index of reliable change will be calculated for each measure using the criteria of Jacobson and Truax [46]. Findings will be analyzed in terms of standardized mean differences and effect sizes achieved will be compared to existing high quality trials to determine relative efficacy of this intervention. Multivariable multilevel models will also explore other covariates on the relationship between treatment arm and study outcomes, with a view to improving the intervention and specifying its ideal target population. Data will be stored in a locked cabinet, and a password protected computer file will contain de-identified (coded) data. A proportion of the data will be double-entered, and range checks will be performed for accuracy checking. Intention-to-treat analysis will be used with the last observation carried forward as a conservative estimate of outcome when data are missing at follow-up.

In addition, analysis of qualitative data from the transcribed interviews of participants who did not take up the option of treatment following intake/assessment, discontinued treatment, or completed treatment will be undertaken. Thematic analysis of participants’ accounts of their experience of the intake/assessment process and reasons for either engaging with or distancing themselves from the treatment offered will be undertaken. Meanings participants assign to the process will also be extracted from the data. Analysis of the data relevant to the phenomena of interest will assist in the identification of barriers to engagement and change for families.

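### The primary outcome is binary remission, but the trial is sized from d = 0.63 in symptoms, and the stated remission equivalent (14% higher odds) contradicts that d; the 90% power is not supported for remission

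*Protocol article*

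**What the plan says.** The Overview fixes the endpoint: "The primary outcome measure will be rates of remission of depressive disorder (major, minor, or dysthymia"), assessed by structured interview. Under Aims and hypotheses, the primary hypothesis is that youth given BEST MOOD will show "significantly greater rates of remission of depressive disorders (major, minor, or dysthymia), than youth in the PAST intervention". The Statistical analysis plan section matches a binary endpoint: "Repeated measures binomial data will be analyzed over three time points using a binary logistic regression", within a generalized linear mixed model.

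Sample size and power starts from a different scale, a standardized effect of d = 0.63 "in reduction of mental health symptoms". It links this to remission in one clause, "which is equivalent to 14% increase in the odds of remission [45"], and adds that in pilot data the "treatment type by time interaction is able to produce up to 50% remission in depression diagnosis, over and above treatment type". It then continues "With an alpha of 0.05 and power level of 0.90 for two-tailed tests", a therapy-group ICC of 0.17 and 10% of the variation in the main outcome explained by other model terms, and arrives at 57 per arm. With attrition of 20-25%, 80 per arm are to be recruited. A separate paragraph covers the continuous secondary outcomes (d = 0.23, therapy-group ICC 0.07).

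**The concern.** A standardized mean difference and a difference in remission proportions are different inputs. Dichotomizing loses information, so the same underlying effect usually needs more participants when it is read as yes/no. The section gives no pair of remission proportions, so a reader cannot check the 90% against the primary endpoint. The one figure offered as a remission equivalent is far too small to belong to d = 0.63.

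At stake is how the primary result will be read. If 90% power is taken to apply to remission, a null result will look more conclusive than it is.

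**Working it through.** **Inputs from the protocol article:** d = 0.63; two-sided alpha 0.05; power 0.90; 57 per arm evaluable; 80 per arm recruited; attrition 20-25%; therapy-group ICC 0.17; 10% explained variation. **Assumed, because not stated:** PAST remission of 20-50%; families per therapy group m = 2, 4 or 8.

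**1. The plan's own figure.** For two means, n = 2 × (1.96 + 1.2816)² / 0.63² = 52.9 per arm, or 54 with the t distribution. Neither is 57. Applying the stated modifiers, 54 × [1 + (m − 1) × 0.17] × 0.90 gives:
- m = 2: 54 × 1.17 × 0.90 = 56.9, that is 57
- m = 4: 54 × 1.51 × 0.90, about 73
- m = 8: 54 × 2.19 × 0.90, about 106

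So 57 can be reached from a continuous-outcome formula, but only with an assumed m = 2. How it was actually obtained is not established.

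**2. The bridge to remission.** The logistic conversion is ln(OR) = d × π/√3 = 0.63 × 1.814 = 1.143, so OR = exp(1.143) = 3.14. That is a 214% increase in the odds, not 14%. In the other direction, OR 1.14 corresponds to d = ln(1.14) × √3/π = 0.07. The log odds ratio happens to be 1.14, so a log odds ratio read as an odds ratio would explain the 14%. The document does not show whether that happened.

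**3. Power for remission at 57 per arm, no clustering, no covariate credit.** With p1 for PAST, p2 from OR 3.14 and p̄ their mean, power = Φ{[(p2 − p1)√n − 1.96 √(2p̄(1 − p̄))] / √(p1(1 − p1) + p2(1 − p2))}. Example for p1 = 0.30: p2 = 0.573, p̄ = 0.437, and (0.273 × √57 − 1.96 × 0.701) / 0.674 = 1.02, so power is 84.6%.

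| PAST remission (assumed) | BEST MOOD remission | Power at 57 | n per arm for 90% |
|---|---|---|---|
| 20% | 43.9% | 79.0% | 78 |
| 25% | 51.1% | 82.8% | 71 |
| 30% | 57.3% | 84.6% | 68 |
| 35% | 62.8% | 85.3% | 66 |
| 40% | 67.6% | 85.1% | 67 |
| 50% | 75.8% | 82.3% | 72 |

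Outside this range power is lower: 59.9% at PAST remission of 10% and 76.2% at 60%. With OR 1.14 it is about 5% throughout.

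**4. Adding the stated modifiers.** Effective n = 57 / {[1 + (m − 1) × 0.17] × 0.90}, over PAST remission of 20-50%:
- covariate credit only: 57/0.90 = 63.3, power 83-89%
- m = 2: 57/(1.17 × 0.90) = 54.1, power 77-83%
- m = 4: 57/(1.51 × 0.90) = 41.9, power 66-73%
- m = 8: 57/(2.19 × 0.90) = 28.9, power 50-56%

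**5. Using the numbers left after attrition.** 80 × 0.75 = 60 and 80 × 0.80 = 64. With the covariate credit and no clustering, power is 85-92%. Even in the most favourable clustered case, 64 per arm and m = 2, effective n is 64/(1.17 × 0.90) = 60.8, below the smallest requirement in the table (66).

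**The case against.** The strongest reply is that the authors did not ignore remission. They offer a conversion, cite pilot remission and refer to the main outcome, so it goes too far to say that the calculation simply concerns another endpoint. That stands as a point of fairness, but it does not rescue the figure: the conversion offered is the part that contradicts d = 0.63, and the pilot remission statement is not split by arm.

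A second reply is that 79-85% is not the power of this trial. It depends on an assumed PAST rate and one conversion, and it leaves out the ICC and the covariate credit. This also stands. Two other conversions (1.65 × d, and a shift on the normal scale) give lower values, 70-78% and 71-76% without clustering. With 60-64 evaluable and the covariate credit but no clustering, the range spans 90%. That case, however, drops the ICC that the section itself includes. The credit is also generous, because the terms listed for it include treatment arm and time.

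Third, the planned analysis is a mixed logistic model over three time points, which a single-time comparison does not represent. That is a real limit on precision. But every adolescent must meet criteria for a depressive disorder at entry, so the baseline assessment carries no between-arm information on remission.

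A reader might also infer that 57 came from a plain t-test that ignored clustering, because 54 is close. The document does not support that: it names the ICC and the explained variation as inputs, and 57 is not reproduced without assuming a group size.

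**Conclusion.** The point holds in conditional form. The primary sample size rests on an effect in symptoms, no remission proportions are given, and the stated remission equivalent is inconsistent with the stated d. Under the logistic conversion, no PAST remission rate tried brings 57 per arm to 90%. The best case is about 85% with neither modifier and about 89% with the covariate credit alone. With the stated ICC the shortfall is larger, by an amount that depends on the unstated group size.

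Two stronger readings should be resisted. One is that the trial has 79-85% power: that range is an illustration under assumed PAST remission of 20-50% and independent observations. The other is that it has about 5% power: that follows only if the 14% is taken literally, and the clash with d = 0.63 suggests that the 14% is a misstatement and not the design effect.

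**What to change.** In Sample size and power:
- State the assumed remission proportions for PAST and BEST MOOD, with their source, and the assumed number of families per therapy group.
- Correct the statement of a 14% increase in the odds so that it agrees with the effect used.
- Restate the power for remission at the planned size, with the ICC of 0.17 included and the covariate credit shown as a separate step.
- Leave the secondary-outcome calculation (d = 0.23) unchanged. It is a separate calculation, and d = 0.63 should not be moved into it.

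The cost is a rewritten paragraph and a short recalculation from pilot data. Correcting the figure requires no change in enrolment.

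### The stated 90% power to detect d = 0.23 for the arm-by-time interaction with 114 participants does not follow from the protocol's own inputs

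*Protocol article*

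**What the plan says.** The second paragraph of Sample size and power in the protocol article turns from the primary outcome to the secondary hypotheses. It takes an "anticipated final sample size of 114 individuals", which is the 57 per arm of the preceding paragraph, and says that this number "will also allow us to detect small effect size (d = 0.23) for the treatment arm by time interaction for continuous outcomes". The power claimed for this is 90% at an alpha of 0.05. The correlation inputs follow in the same sentence: "assuming ICC of 0.20 for within-person (between-assessment) and ICC of 0.07 for within therapy group variation". No formula, therapy-group size or definition of d for an interaction is given. Two-sided testing is stated only for the primary calculation ("With an alpha of 0.05 and power level of 0.90 for two-tailed tests"). The abstract gives equal allocation and three assessments: baseline, eight weeks and 20 weeks. The Statistical analysis plan section assigns continuous outcomes to a linear mixed model.

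**The concern.** With 57 per arm, a plain comparison of two means at one visit detects about 0.61 SD at 90% power. Repeated measures can improve on that, but a within-person correlation of only 0.20 leaves little to gain. It makes a change score noisier than a single measurement, with variance 2(1 − 0.20) = 1.6 against 1. A detectable interaction of 0.23 from the same sample therefore looks too small by a wide margin.

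At stake is secondary hypothesis (a), that parental and youth mental health and relationships improve more under BEST MOOD. For its continuous measures this hypothesis rests on the arm-by-time interaction. A reader who trusts the statement could take a null result as evidence against a benefit of 0.23 SD, when the trial had limited power to see one.

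**Working it through.** **Inputs from the protocol article.** 114 analysed, 57 per arm; power 90%; alpha 0.05; within-person correlation ρ = 0.20; three assessments; therapy-group ICC 0.07.

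**Assumptions.** Two-sided test, carried over from the primary calculation. Equal variance at each visit (SD = 1) and equal correlation between visits. No clustering at first, which favours the plan or is neutral.

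**1. Contrasts with one degree of freedom.** Detectable effect = (1.960 + 1.2816) × √(2V/57) = 3.2415 × √(2V/57), where V is the per-person variance of the contrast.

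| Contrast | V at ρ = 0.20 | Detectable at 90% | Multiple of 0.23 | Power at 0.23 |
|---|---|---|---|---|
| Change from baseline | 2(1 − ρ) = 1.60 | 0.77 | 3.3 | 16% |
| Mean of two follow-ups minus baseline | 1 + (1 + ρ)/2 − 2ρ = 1.20 | 0.67 | 2.9 | 20% |
| One follow-up, baseline-adjusted | 1 − ρ² = 0.96 | 0.60 | 2.6 | 24% |
| Mean of two follow-ups, baseline-adjusted | (1 + ρ)/2 − ρ² = 0.56 | 0.45 | 2.0 | 37% |
| Linear slope per wave (times 0, 1, 2) | (1 − ρ)/2 = 0.40 | 0.38 | 1.7 | 49% |

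For the first row, 3.2415 × √(3.2/57) = 0.768. The slope of 0.38 is per wave, so it equals 0.77 SD over the two waves.

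**2. Interaction F test with 2 df.** Noncentrality λ = f² × 114 × 3/(1 − 0.20), with 2 and 224 degrees of freedom. Power of 90% needs f = 0.173.
- By the convention d = 2f this is 0.35, or 1.5 times 0.23. At f = 0.115 (d = 0.23 by that convention) power is 55%.
- The convention is not on the scale of a difference in change. If the arms are equal at baseline and differ by δ at both follow-ups, f = δ/√18 = 0.236δ. Then f = 0.173 means δ = 0.173/0.236 = 0.73 SD, and a true δ of 0.23 has about 15% power.

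**3. Attempts to reproduce 0.23 at ρ = 0.20.** In all of these the detectable effect stays above 0.23. On the slope, the smallest of the one-df contrasts in the table, one-sided testing gives 0.35, 80% power gives 0.33 and 114 per arm gives 0.27. Doubling the sample for the F test gives about 0.346/√2 = 0.24 by d = 2f.

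**4. Readings that do come near 0.23, each departing from the text.** Where group sizes appear in this step, all variances are inflated by 1 + (m − 1)0.07.
- *0.23 is Cohen's f.* The F test needs f = 0.173 without clustering and 0.230 with assumed groups of 12. But f = 0.23 is d = 0.46 by d = 2f, or 0.23 × √18 = 0.98 SD of differential change under the pattern in step 2.
- *The correlation is 0.80, with 0.20 the within-person share of variance.* The slope per wave is 0.19 without clustering and 0.234 with groups of 8. The F test by d = 2f is 0.173 without clustering and 0.230 with groups of 12. Change from baseline is still 0.38 without clustering.

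**5. Therapy-group clustering.** Its effect depends on the contrast. A group effect that is stable over time cancels from a change score, leaving 0.77. If group variance of 0.07 arises only after baseline, V rises by 0.07(m − 1). Group size m is not given. With an assumed m = 6, change becomes 3.2415 × √(2 × 1.95/57) = 0.85 and the baseline-adjusted mean of two follow-ups 3.2415 × √(2 × 0.91/57) = 0.58. With m = 12 they are 0.93 (V = 2.37) and 0.70 (V = 1.33).

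**The case against.** The best defence is that d is undefined for an interaction and the wording of the 0.20 ICC is unusual, so the authors may have computed something coherent and described it loosely. Step 4 shows two such routes. This stands as a possible explanation, but the text says d and gives 0.20 as an ICC, conventionally the correlation between assessments. A reader might infer that 0.23 must be a mislabelled f. The document does not establish that, because the 0.80 correlation fits as well.

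A reader might also condense the result to a detectable effect two to three times the claim, with power of 16% to 38%. That is too neat. The F test, which is the nearest match to the test named, gives 1.5 times and 55% by d = 2f, while change from baseline gives 3.3 times. The scales also differ: 0.35 by d = 2f, 0.38 per wave and 0.77 in change cannot be ranked as if they were one quantity.

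Nor can one say that the 0.07 ICC worsens every figure by 1 + (m − 1)0.07. For change contrasts that depends on whether the group effect is already present at baseline.

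Finally, the claim covers continuous outcomes only (group attendance, one engagement measure, is yes or no) and did not set the sample size. The plan also reports standardised effect sizes, so misreading of null results is a risk and not a certainty. These points limit the weight of the finding. None of them restores 0.23.

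**Conclusion.** The power statement for the continuous secondary outcomes is wrong as written. Under its stated sample size and within-person ICC, two-sided and before any clustering, the effect detectable at 90% power is about 1.5 to 3.3 times 0.23, and power at 0.23 is about 15% to 55%. The spread comes from the missing definition of d. On the SD scale of differential change the figures are 0.67 to 0.77, and with baseline adjustment 0.45 to 0.60.

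The result rests on reading 0.20 as the correlation between assessments, equal variances and correlations across visits, and two-sided testing. Clustering figures need a group size that the document does not give. A reader might infer that the primary sample size fails too, but this check does not bear on it: that calculation concerns remission and uses a different ICC.

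**What to change.** Restate the secondary detectable effect, or the power at 0.23, for the contrast the linear mixed model will actually test. Give:
- the effect metric (difference in change, baseline-adjusted difference, slope per wave, or f);
- what the 0.20 ICC means (correlation between assessments or share of variance);
- the assumed therapy-group size, with clustering handled to suit that contrast and not by a blanket 1 + (m − 1)0.07 on change scores;
- the sidedness of the test.

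Drop the word small if the restated effect is not small. If a different metric or correlation lies behind 0.23, saying so and showing the formula would settle the matter.

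The cost is a change of protocol wording and a less favourable stated figure. The primary sample size, the procedures and the primary analysis are unaffected.
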